## **2.4.7 Procedure**

### **2.4.7.1 Data collection**

Ethical approval, permissions and consent would be obtained during season one before conducting the study. Translation of the questionnaires into Kinyarwanda will be done before the pilot study. The translated questionnaires will be piloted among licensed five soccer coaches at school level to assess for clarity and responsiveness. A meeting will be held with them to discuss any unclear question from the translated versions and possibilities for better refining them.

During the preseason period, questionnaires assessing the knowledge of coaches regarding injury prevention will be distributed to coaches and appointment will be made for collection of the filled questionnaire. Questionnaires will be collected either by the researcher or the research assistants. Information pertaining to the availability of the medical personnel will also be obtained from the questionnaires.

Because of the changes that might take place at the end of the first season, coaches will again be invited to answer the knowledge questionnaires that will be distributed to them during the preseason period. Any other changes that will take place will also be noticed before the start of the season 2015-2016 as to the arrival of the new or change of the coaches, new teams registering into the second division league or new medical personnel arriving into the teams.

During the preseason period, July-August 2015, all the head, assistants and goalkeeper coaches of the teams in the intervention group in the second division will be invited to the training. The first part of the training will be conducted in two days where they will be taught about injury prevention in general and more specifically the importance and the use of the “11+” warm up programme. The first day will be for introduction and theoretical explanation of the conduct of the “11+” exercises while the second day will be reserved for practical demonstrations. The training will be provided by the researcher. Coaches will also be introduced to the recording of the use of the exercises while in the teams. The recording will be emphasized to ensure compliance. At the end of the training, the coaches will be provided DVDs, pamphlets and the FIFA link (where they could download the materials for free) of the exercises and will be

requested to use the “11+” as the warm up programme at least three times a week and before each match that the team will play.

Coaches will also be trained on first aid. During the training, they will receive the first aid course for two days that will be provided by the trainer from the Rwanda Red Cross. Questionnaires will be distributed to the coaches to assess their knowledge immediately after first aid training. At the end of season two (June 2016) questionnaires will be distributed to the coaches from both divisions to assess the knowledge retained after one year of intervention.

Coaches and medical personnel from the first division will be requested to continue the recording of injuries and exposure using the procedure they used in the season one (2014-2015). To increase compliance and proper recording, coaches will be visited at team practice by the researcher to see if proper implementation is occurring and additional instructions on the correct conduct of the exercises will be provided where necessary. Data collection during season two (2015-2016) will be the same as season one where players exposure time, occurrence of injuries, treatment will be assessed.

Figure 3: Study two framework

[figure not shown]

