#### **2.4.1.1 Objectives**

- a. To assess if there is an increase in the knowledge of coaches towards injury prevention before and after the intervention
- b. To assess if there is any difference in perception of the soccer coaches towards injury prevention before and after intervention
- c. To assess whether the introduction of an injury prevention programme will increase the readiness for injury prevention practice of soccer coaches

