### **2.4.5 Pre- and post-tests**

#### **2.4.5.1 Knowledge assessment questionnaire**

Questionnaires will be distributed to the coaches to assess their knowledge and belief related to injury prevention. Furthermore, coaches' readiness for injury prevention practice will be assessed prior to the intervention (Appendix K). The questionnaire will be comprised of 4

sections: section A will assess the demographic characteristics of the coaches including the age, highest coaching qualification, highest academic qualification, number of years coaching, number of years coaching first/ second division teams and number of years in the current team. In this section, they will also be asked whether they have received any first aid or injury prevention training. Section B assesses availability of the medical care in the team. Section C assesses injury prevention belief and practice readiness in key areas like planning injury prevention practice, use of protective equipment, checking playing field and facilities and up to date information. Section D assesses the first aid knowledge.

The validity and reliability of the questionnaire was established in a study conducted among high school coaches. The validity of the questionnaire was established during the two stage Delphi methods while the test-retest reliability was done to ascertain its reliability. Constructs pertaining to the stage of change, perceived susceptibility, benefits and self-efficacy were all Cronbach's alpha 70% and above (Siwon, 2013).

Looking at the fact that the knowledge constructs yielded a 39% Cronbach's alpha. An additional questionnaire used to assess the first aid and injury prevention knowledge was added to the previous one. The questions were developed by the American Red Cross after completion of first aid and sports injury courses to assess the gained knowledge. Participants were required to score minimum 80% to obtain certificates.

The questionnaires originally written in English will be translated in Kinyarwanda. Kinyarwanda is the national language which is spoken by all the Rwandan people. The questionnaire will be translated into Kinyarwanda by the researcher and the expert from the Rwanda Red Cross. The Kinyarwanda questionnaire will then be back-translated into English by a professional translator. It will then be piloted among five coaches in schools. The consensus meeting will be held to discuss the divergent areas in the two versions.

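### The first coach knowledge pre-test is taken away and collected later, the post-test is handed out straight after the course, and no common test conditions are set, so the before-after change may mix learning with a change in conditions.

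*Combined protocol and SAP*

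**What the plan says.** The objective at stake is Aim 1, objective a (2.4.1.1): "To assess if there is an increase in the knowledge of coaches towards injury prevention before and after the intervention".

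The measure is described in 2.4.5.1. The knowledge part of the source questionnaire had a Cronbach's alpha of only 39%, so further items were added. On their origin the section says: "The questions were developed by the American Red Cross after completion of first aid and sports injury courses to assess the gained knowledge". On the layout of the form it says: "Section D assesses the first aid knowledge".

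Section 2.4.7.1 covers administration. The first preseason questionnaires "will be distributed to coaches and appointment will be made for collection of the filled questionnaire". For the post-test it says: "Questionnaires will be distributed to the coaches to assess their knowledge immediately after first aid training". The same section also describes a second preseason round and a round in June 2016.

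**The concern.** First aid questions of this kind have right and wrong answers. A coach who keeps the form until a collection appointment can look answers up or fill it in with a colleague. Conferring is easy, because 2.4.4.1 enrols head, assistant and goalkeeper coaches of the same team. A coach who answers straight after a course, with the class still assembled, has less chance to do either.

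If conditions differ between rounds, the difference in conditions goes straight into the change score. It is a bias, so more coaches would not remove it, and it cannot be separated from learning once the data are in. Section 2.4.8 also correlates first aid knowledge with compliance, so a score distorted by test conditions would enter that analysis too. The injury outcome is not affected.

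**Working it through.** The plan gives no figure to reproduce: there is no mean, standard deviation or sample size for coach knowledge. The sample size in 2.4.4.3 concerns player injuries. The check is therefore mainly a comparison of the rounds, all taken from 2.4.7.1.

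| Round | What is stated | What is not stated |
|---|---|---|
| First preseason round | Handed out, returned by appointment. "Questionnaires will be collected either by the researcher or the research assistants" | Any staff presence during completion |
| Second preseason round, before season 2015-2016 | "coaches will again be invited to answer the knowledge questionnaires that will be distributed to them during the preseason period" | How it is completed and returned |
| Immediately after the first aid course | Handed out to the coaches at that point | Whether it is completed on site, supervised or without materials |
| June 2016 | "questionnaires will be distributed to the coaches from both divisions to assess the knowledge retained after one year of intervention" | How it is completed and returned |

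Three things follow. Only the first round has a stated take-away mode. No round is said to be supervised, timed or free of reference material. The text does not say which of the two preseason rounds is the baseline.

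**Direction of the effect.** Let K0 and K1 be true knowledge before and after training. Let b0 and b1 be the points added at each round by look-up or sharing.

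Observed change = (K1 + b1) − (K0 + b0) = (K1 − K0) − (b0 − b1).

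- Pre-test taken away, post-test on site without materials (b0 > 0, b1 = 0): the gain is understated by b0.
- Both taken away, with the same shift (b0 = b1): the effect cancels.
- Pre-test supervised, later round taken away (b0 = 0, b1 > 0): the gain is overstated by b1. This could arise in June 2016 if only the baseline were supervised.

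**Illustration only.** Every input here is an assumption; the documents supply none. Let p be the share of items truly known and L the share of unknown items that are looked up. The observed score is then p + L(1 − p). Take p = 0.50 before and 0.80 after, a true gain of 30 points.

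| L | Pre-test reads | Gain if post-test has no look-up | Post-test reads with the same L | Gain if both have the same L |
|---|---|---|---|---|
| 0 | 0.50 | 30 points | 0.80 | 30 points |
| 0.2 | 0.50 + 0.2 × 0.50 = 0.60 | 20 points | 0.80 + 0.2 × 0.20 = 0.84 | 24 points |
| 0.5 | 0.50 + 0.5 × 0.50 = 0.75 | 5 points | 0.80 + 0.5 × 0.20 = 0.90 | 15 points |

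Under this model, equal look-up at both rounds leaves (1 − L) of the true gain. Cancellation is therefore close to complete when look-up is light and partial when it is heavy. The table shows how the answer depends on facts that the plan does not fix. It does not estimate the bias.

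**The case against.** The strongest reply is that a reader might infer an open-book pre-test set against a closed-book post-test, and the documents do not say that. The post-test is distributed, just as the pre-test is, and nothing places its completion in the classroom or bars materials. Coaches also receive DVDs and printed material at the end of the 11+ training. This stands: the mode difference is possible, not established.

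The take-away round may also not be the baseline. The second preseason round is closer to the 2015 training and its mode is not given. This stands too, and it is why the baseline must be named.

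A reader might take the 80% score in 2.4.5.1 as an incentive to look answers up. It describes the source courses and their certificates; the text attaches no pass mark to this trial's questionnaire.

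A reader might also infer that trained coaches gain a practice advantage by June 2016 from one extra sitting. That assumes control coaches are not trained in first aid, and the documents conflict on this. Section 2.2 says control-team coaches will receive first aid training, and 2.4.4 counts at least 19 coaches, one per second-division team, as receiving the training. Sections 2.4.6 and 2.4.7.1 invite only the intervention group. Moreover, the knowledge ANOVA in 2.4.8 compares divisions, not arms.

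Understating a gain is the conservative direction, and the belief and readiness items cannot be looked up. Both points are fair and limit the concern to the factual items. Finally, Appendices J and K and Figure 3 are not in the text reviewed, so completion instructions may exist there.

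What remains is that the plan states a take-away mode for one round of a factual test and requires no common conditions for the others.

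**Conclusion.** The concern holds in a limited form. As written, 2.4.7.1 lets the knowledge rounds be completed under different conditions, and the before-after change in Aim 1, objective a, may then mix learning with that difference. If the post-test is completed on site, the likely effect is an understated immediate gain. If both rounds are taken away, the effect may largely cancel. The size is unknown, and the documents do not support any statement of how much of the effect would be lost.

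The conclusion rests on two assumptions: that some coaches would look up or share answers when unsupervised, and that no appendix already sets the conditions. It touches only the factual knowledge score. It is worth acting on because supervised completion is a better method than the one stated and costs little, and because the bias cannot be corrected after the baseline has been collected.

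**What to change.** Change 2.4.7.1 as follows, and carry any completion instructions into Appendix K.

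- Name the 2015 preseason round, before training starts, as the baseline for objective a. Define it relative to the course rather than by month, because the training is dated October 2015 in 2.4.6 and July-August 2015 in 2.4.7.1; those dates must be reconciled.
- Have the knowledge questionnaire at every round (preseason, immediately after training, June 2016) completed individually, without materials, in one sitting with study staff present.
- Use the same conditions and the same timing window in both arms at the rounds that both arms sit.
- At the course, have the researcher supervise. The researcher is already unblinded under 2.4.4.5, whereas a research assistant would learn both the allocation and the type of intervention.

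Staff already hand out and collect the forms, so the cost is the time to stay while they are completed, and less flexible timing for coaches. An extra sitting for control coaches is not needed for this fix. Whether control coaches receive first aid training has to be reconciled between 2.2 and 2.4.4 on one side and 2.4.6 and 2.4.7.1 on the other before that question can be considered.

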#### **2.4.4.1 Inclusion criteria**

Head coaches and their assistants as well as goalkeeper coaches of the teams participating in the second division league will be included in this study. Players who have contracts and licenses of teams enrolled to play in the second division will be included in the study. Players presenting injury at the beginning of the study will be included when cleared to join teams' training and matches. Players with injuries at the start of the study will be included, but the pre-existing injuries will not be included in data analysis. Players or teams that will leave or join the league before the end of the study will be included in the analysis for their time of participation.

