#### **2.4.4.5 Blinding**

The teams are organized in such a way that coaches are the ones planning all the activities to be performed by the players. In this study they are the ones responsible for implementing the intervention programme. Therefore, it is not possible to blind the coaches or the players to the allocation of the teams in either the intervention or the control group. The researcher will not be blinded to team allocation but the research assistants will be blinded to team allocation as each assistant will be assigned to one team without any information about whether the team is in the intervention or control group. Research assistants will not know the type of intervention provided to the coaches.

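### The June 2016 knowledge-retention test is not tied to the coaches who were trained, and the available text does not follow trained coaches who leave

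*Combined protocol and SAP*

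**What the plan says.** Section 2.4.7.1 sets out the sequence for coaches.

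- **Baseline.** Knowledge questionnaires are given out in preseason, and again before 2015-2016 because coaches may have changed.
- **Training.** "all the head, assistants and goalkeeper coaches of the teams in the intervention group in the second division will be invited to the training".
- **Immediate test.** "Questionnaires will be distributed to the coaches to assess their knowledge immediately after first aid training".
- **June 2016.** "questionnaires will be distributed to the coaches from both divisions to assess the knowledge retained after one year of intervention".

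The same section expects changes of personnel, which are to be "noticed before the start of the season 2015-2016 as to the arrival of the new or change of the coaches". It gives no matching step for the season itself. The rule on leavers and joiners in section 2.4.4.1 reads "Players or teams that will leave or join the league before the end of the study will be included in the analysis", limited to their time of participation; it does not mention coaches.

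Section 2.4.1.1 asks whether coach knowledge rises from before to after the intervention. For knowledge, section 2.4.8 names descriptive statistics, Pearson correlations (including with compliance) and an ANOVA between the two divisions. It refers to Appendix J for the details.

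**The concern.** Retention is a property of a person who was taught something and is tested again later. As written, the June 2016 test is addressed to coaches of both divisions, although under section 2.4.7.1 neither first-division coaches nor second-division control coaches attend the course. Nothing in the available text says which respondents form the retention group, that a coach's June score is compared with the same coach's earlier score, or what happens to a trained coach who has left by then.

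What is at stake is mainly the coach-knowledge result. If the coaches tested in June are not those tested after the course, a change in mean score mixes forgetting with change of person. If leavers differ from stayers, the result is also selected. June falls after the second-division season, which section 2.3.4 places in November to May, so a trained coach may be hard to reach unless followed individually.

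There is a second, smaller consequence. Of the coaches, section 2.4.4.5 says: "In this study they are the ones responsible for implementing the intervention programme". They also complete the compliance forms (2.4.7.2). Without dates of coach changes, the correlation of knowledge with compliance may pair one coach's score with another's records.

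**Working it through.** The plan states no figure for retention, so there is none to reproduce. The check is a head count, a look at what the ANOVA estimates, and a date calculation.

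**1. Who could show retention if nobody moved**

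Inputs: 14 first-division and 19 second-division teams (2.3.4); nine or ten teams per group (2.4.4.4); training for intervention teams only (2.4.6, 2.4.7.1). Assumption: one head coach per team. Section 2.4.4 says at least one for the second division; for the first division it is assumed. Assistant and goalkeeper coaches are left out because their numbers are not given.

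- Head coaches in both divisions: 14 + 19 = 33.
- Trained: 9/33 = 27%, or 10/33 = 30%.
- Not trained: 24/33 = 73%, or 23/33 = 70%.

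Two other statements conflict with this input. Section 2.2 mentions first aid training for control-group coaches, and section 2.4.4 counts at least 19 coaches as receiving the training. If all 19 second-division head coaches were trained in some form, the share would be 19/33 = 58%, and the 14 first-division coaches (14/33 = 42%) would still have nothing to retain.

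**2. With in-season turnover**

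The documents give no turnover figure, so t is an assumption. If leavers are not followed, the trained share of the June head-coach sample is k(1 - t)/33, with k = 9 or 10.

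| Assumed t | k = 9 | k = 10 | Share within intervention arm |
|---|---|---|---|
| 0% | 27% | 30% | 100% |
| 10% | 25% | 27% | 90% |
| 20% | 22% | 24% | 80% |
| 30% | 19% | 21% | 70% |
| 50% | 14% | 15% | 50% |

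The main loss is already there at t = 0. Turnover adds to it.

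**3. What the stated ANOVA estimates**

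Trained coaches are 9/19 = 47% or 10/19 = 53% of second-division head coaches. Suppose training raises the mean score by D and the divisions are otherwise alike. The difference between divisions is then about 0.47D to 0.53D, roughly half the training effect. The divisions are not randomised against each other, so any existing difference in coaching background is added to that. A comparison at one time point also cannot show change within a coach. The contrast therefore answers neither the retention question nor the before-after objective in 2.4.1.1.

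**4. The interval**

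- Training in October 2015 (2.4.6): from 31 October to 1 June is 7 months; from 1 October to 30 June is 9 months.
- Training in July-August 2015 (2.4.7.1): from 31 August to 1 June is 9 months; from 1 July to 30 June is 12 months.

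One year is reached only at the far end of the second range.

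**The case against.** Several points on the other side are fair.

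- **Untrained coaches as comparators.** A reader might infer that first-division coaches and replacements will be counted as retained knowledge. The documents do not say so. No pooled retention estimate is described, and because section 2.4.8 compares divisions, first-division coaches can be read as a comparison group. Nor does the text say that the June test goes to whoever holds the post then; the coaches meant could be the original ones. This stands, but the text settles neither point.
- **Newcomers can be recognised.** Section A of the questionnaire (2.4.5.1) asks for "number of years coaching first/ second division teams and number of years in the current team", and about earlier first aid or injury prevention training. If it is reused in June 2016, an untrained replacement could be flagged. It cannot recover a trained coach who has left.
- **Programme lapse is visible.** A reader might infer that a programme fading after a coach leaves could not be told from a programme that does not work. That goes too far. Use of the 11+ and the number of players taking part are recorded (2.4.7.2), the researcher visits twice a week (2.4.6), and compliance is to be related to injuries (2.4.2.1). A lapse would show; only its cause would be unlogged.
- **Unavailable material.** Appendices J and K and Figure 3 were not in the text available for this review. A paired analysis or a rule for leavers could be in Appendix J.
- **Weight.** Retention is not a listed objective, and Aim 1 is exploratory. That limits the importance of the point, but the June 2016 questionnaire has no other stated purpose.

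**Conclusion.** The concern holds for the coach-knowledge outcome. On the available text, the June 2016 test would not give a valid estimate of retention: the group is undefined, a coach's tests are not linked, trained leavers are not followed, and the only between-group test pools trained with control coaches. With one head coach per team and training confined to intervention teams, 9 or 10 of 33 head-coach respondents could show retention even with no turnover. This is more than missing detail, because dates of change and contact with leavers may not be recoverable afterwards. The conclusion is conditional on Appendix J not already covering it.

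The one-year label is unsettled rather than plainly wrong, since the interval depends on which training date applies.

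A reader might also infer a diluted injury effect. The documents do not support a figure for this. With assumed in-season turnover f of 10% to 30%, changes at mid-season on average, complete lapse of the programme, and a true rate ratio of 0.65 (a cited study's result in section 1.1, not this trial's planning value), the formula 0.65(1 - f/2) + f/2 gives 0.67 to 0.70. Every one of those inputs is assumed, and assistant and goalkeeper coaches, where a team has them, are invited to the same training. Contamination by a trained coach moving to a control team is possible, but its frequency is unknown.

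**What to change.** 1. In 2.4.7.1 and 2.4.8, define retention as the within-coach change from the immediate post-training test to June 2016, among coaches on the training attendance list, paired by the numeric code that 2.3.10 already assigns to participants. Analyse the before-after objective within coach in the same way, from the 2015 preseason questionnaire to the immediate test.
2. Try to give trained coaches who have left the same self-completed questionnaire, so that the mode of testing does not change, and report how many were lost.
3. Report replacements, second-division control coaches and first-division coaches separately, as comparators.
4. Log each coach arrival, departure and move with its date at the existing two-weekly form collection. Recording code and date only, without training status, leaves the blinding of research assistants in 2.4.4.5 untouched.
5. Keep each team in its allocated arm for the injury comparison, whatever happens to its coach.
6. Reconcile the training dates in 2.4.6 and 2.4.7.1, and the statements in 2.2 and 2.4.4 on who is trained. Then state the actual interval in place of one year.
7. If Appendix J already covers any of this, bring the main text into line with it.

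The cost is one extra line on a form already collected, a little follow-up work for leavers, and text changes. The downside is a smaller retention analysis: about 9 or 10 head coaches, plus any assistants and goalkeeper coaches who attended. It should be presented as an estimate with its confidence interval.

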Player exposure forms will then be provided to the coaches and will be requested to record every training time that each player participate in soccer activities. Because coaches are focusing on the game during the match, it could be hectic for them to record match exposure. For this reason, match exposure will be obtained from the reports that are submitted by the referee to the FERWAFA.

Before the beginning of each season the FERWAFA set a deadline for the teams to submit the list of all the players that they will use in the league. Therefore the list of all the players will be obtained from the FERWAFA while additional information pertaining to the study will be requested from the team management.

All the medical personnel of the teams will be invited into the briefing meeting that will be held at the FERWAFA premises to explain to them about the study and their task in the study. They will be explained how to fill the injury report forms and they will be asked to report any injury that will take place during data collection. The injury report and exposure forms will be collected by the researcher or the research assistants after every two weeks.

Training and match exposure as well as injury recording for the main study will commence one week before the first game because training performed during that week is for the preparation of the first game. The first division season will start in September 2014 while the second division season will start in November 2014. The exact dates will be obtained from the FERWAFA after the general assembly meeting preparing the league that will take place after the season 2013-2014. Data collection will take place throughout the season up to the last game. Because the FERWAFA allows the teams to recruit new players during the mid season, players who will join the teams halfway through will be recorded from the period recruited. The season will end in June 2015 for the first division and May 2015 for the second division. At the end of the season, the last two teams from the first division are relegated to the second division while the first two teams in the second division are promoted to the first division. A period of rest is given to the

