##### **The “11+” injury prevention programme**

The intervention programme “The 11+” will be introduced to coaches during the training (Appendix L). Coaches will be instructed on the 15 evidence-based exercises and the promotion of Fair Play. They will be instructed on how the exercises focus on core stability, balance, dynamic stabilization, and eccentric hamstring strength and their effects on frequent injury prevention. On field practical demonstration will also be conducted. At the end of the training, each coach will receive a DVD of the exercises and the total programme instructions and a booklet for reference. Coaches will be instructed to use the training programme at least 3 times a week and at every match and will record dates and times of using the training programme. Coaches will be visited at team practice by the researcher two times a week to see if proper implementation is occurring and additional instructions will be provided where necessary. The intervention will be conducted during the preseason period, October 2015.

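### Twice-weekly visits by the unblinded researcher, partly for recording, are described only for the 11+ programme, so training hours may be captured more completely in that arm

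*Combined protocol and SAP*

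**What the plan says.** Section 2.4.6, in the part on the 11+ programme, sets the frequency of the visits: "Coaches will be visited at team practice by the researcher two times a week". Section 2.4.7.1 returns to them and adds a second purpose: "To increase compliance and proper recording, coaches will be visited at team practice by the researcher to see if proper implementation is occurring". It then says that "additional instructions on the correct conduct of the exercises will be provided where necessary". Neither section describes a corresponding visit to control teams, and section 2.4.9 has those teams keep their usual warm-up.

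On blinding, section 2.4.4.5 states: "The researcher will not be blinded to team allocation but the research assistants will be blinded to team allocation". The assistants are to be kept blind because "each assistant will be assigned to one team without any information about whether the team is in the intervention or control group".

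On the forms, section 2.3.6.1 says: "The injury report and exposure forms will be collected by the researcher or the research assistants after every two weeks". Section 2.4.7.1 carries the season-one data collection into season two unchanged. The comparison between groups is a rate ratio of injuries per 1000 hours (section 2.3.9, applied to study two by section 2.4.8).

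**The concern.** The visits deal with exercises that only the 11+ teams perform, and they are made by someone who knows the allocation. If they also prompt coaches to complete exposure forms, 11+ coaches get about four extra contacts on recording in every two weeks (2 per week × 2 weeks), on top of the form collection that every team has. Control coaches are promised only the collection.

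The coach's training-hours record is part of the denominator of the rate. If it is more complete in one arm because of the trial's own procedures, that arm's injury rate falls with no change in injuries. The visits begin with the intervention, so the before-and-after comparison (aim 2, objective a) is open to the same artefact. The plan also lets the unblinded researcher handle the outcome forms, although an assistant is already assigned to each team.

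**Working it through.** The plan states no figure on this point, so there is none to reproduce. The check is to see which parts of the rate the visits can reach, and then how far a difference in capture would move the rate ratio.

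**Step 1. Who records what**

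| Item | Recorder | Section | Reached by visits to coaches? |
|---|---|---|---|
| Injuries | Team medical personnel, or the research assistant where there are none | 2.3.5.4 | Indirectly at most |
| Training hours | Coach | 2.3.5.3, 2.3.6.1 | Directly, if the visits cover exposure forms |
| Match hours | Referees' reports | 2.3.5.3, 2.3.6.1 | No |
| 11+ use log | Coach | 2.4.7.2, Appendix N | Directly, but it does not enter the rate |

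The indirect route for injuries has three parts. The definition takes in any physical complaint (2.3.5.4). The exposure form also holds absences and their reasons (2.3.5.3). The researcher may collect the injury forms (2.3.6.1).

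**Step 2. Formula**

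Rate = 1000 × injuries / hours (2.3.9). Let k_I be injury capture in the 11+ arm divided by that in control, and k_H the same ratio for hours. Then

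observed RR = true RR × k_I / k_H.

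**Step 3. Training hours only, true RR 1.00**

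Assume, for illustration, that 95% of training hours are captured in the 11+ arm and 85% in control, with injuries captured equally.

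- Training rate alone: 0.85 / 0.95 = 0.89.
- All hours: match hours do not change, so they dilute the effect. Section 2.3.5.3 does not give team totals, so assume them. Match: 11 players × 1.5 h × 12 matches = 198 h per team (section 2.3.4 gives 11 to 12 matches). Training: 3 sessions a week × 26 weeks = 78 sessions. At 20 players and 1 h this is 1,560 h; at 30 players and 1.5 h it is 3,510 h. Training is then 1,560/1,758 = 89% to 3,510/3,708 = 95% of all hours.
  - Low case: (198 + 0.85 × 1,560) / (198 + 0.95 × 1,560) = 1,524 / 1,680 = 0.91.
  - High case: (198 + 0.85 × 3,510) / (198 + 0.95 × 3,510) = 3,181.5 / 3,532.5 = 0.90.

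A true 1.00 therefore appears as about 0.89 to 0.91.

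**Step 4. If injury capture also changes**

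Observed RR for a true RR of 1.00, over assumed capture ratios:

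| k_I | k_H = 1.00 | k_H = 1.10 | k_H = 1.25 |
|---|---|---|---|
| 1.00 | 1.00 | 0.91 | 0.80 |
| 1.10 | 1.10 | 1.00 | 0.88 |
| 1.25 | 1.25 | 1.14 | 1.00 |

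Equal improvement in both gives no bias. As an unequal example, assume injury capture of 95% against 80% (0.95/0.80 = 1.19) together with hours at 95% against 85% (0.95/0.85 = 1.12, ignoring the dilution by match hours). The net factor is 1.19/1.12 = 1.06, and a true 0.80 appears as 0.85. The sign depends on which record improves more, and the documents do not settle that.

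**The case against.** The strongest reply is that the recording meant in section 2.4.7.1 is the 11+ use log. The same sentence speaks of compliance and implementation. Earlier in that section coaches are taught to log use of the exercises, and recording is stressed as a means to compliance. On that reading the visits touch neither numerator nor denominator. This is a natural reading, and it is why the point is conditional. It is not the only one: the sentence stands between one on recording injuries and exposure in the first division and one on exposure and injury collection in season two. A few words would settle it.

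Three further points stand and limit the concern. Coaches do not record injuries; medical personnel do, or assistants who are meant to be blinded. Match hours come from referees, so for the match rate neither part is coach-recorded. Form collection is two-weekly with no difference by arm stated, and season-two collection is to follow season one, although that does not say whether visits are added for some teams.

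A reader might infer that the visits go to 11+ teams and no others. The documents never say so. It is a strong inference from where the visits are described and what they correct, and the sentence in 2.4.7.1 directly follows one about first-division coaches. A reader might also hold that the analysis can do nothing about such a difference. That goes too far: season one supplies exposure records from before the intervention, so a shift in recorded hours in one arm could at least be examined. It could not by itself be told apart from a real change in training time.

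**Conclusion.** The point holds as a risk that the wording leaves open. The visits are twice weekly, made by an unblinded person, partly for recording, and described only with the 11+ programme. The same person may collect the outcome forms, and no matching contact with control teams is described. If the visits cover exposure forms, the most direct effect is more complete training hours in the 11+ arm and so an apparent benefit: about 0.89 to 0.91 for a true 1.00, on the assumed 95% against 85% capture and the assumed team hours.

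The documents do not support the stronger conclusion that injuries and hours are both captured better in one arm and that the rate ratio is therefore biased. Injury capture is reached only indirectly, match hours not at all, and gains in both records would partly or wholly cancel. The rate ratio may be biased, with net size and direction unknown. Because the remedy is cheap, the plan should be changed before season two.

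**What to change.** 1. In sections 2.4.6 and 2.4.7.1, limit the researcher's visits to the conduct of the exercises and the 11+ use log (Appendix N). Replace 'proper recording' with 'proper recording of 11+ use'. Do not simply delete the phrase: if it means the log, deletion would remove on-site checking of data needed for the compliance objective (aim 2, objective b).
2. State that in 2015-16 the researcher does not prompt, check or collect injury or exposure forms at any second-division team. The assigned research assistant does this at the existing two-weekly collection, with the same checklist and schedule in all 19 teams.
3. Report the completeness of training-exposure forms by arm and by season.

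The cost is a change of wording and one added table. No extra staff are needed, because section 2.4.4.5 already assigns an assistant to each team. Keeping the 11+ log with the researcher also avoids showing assistants the allocation through that form. The downside is that the researcher can no longer stand in for an assistant in collecting second-division forms.
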